# **Chapter 1: Introduction to the IMPACT Research Study**

## 1.1 INTRODUCTION

### 1.1.a SUMMARY

The Initiate and Maintain Physical Activity in Clinics (IMPACT) Study is a research study utilizing physical activity in an intervention for Type 2 diabetes (T2DM) patients in a clinical setting. The study will compare structured group exercise within the clinic for T2DM patients compared to usual care, which does not involve structured group exercise within the clinic setting. The main purpose of the study is to determine the optimal and feasible level of frequency of structured contact needed in a clinical setting for adult T2DM patients to initiate and maintain physical activity recommendations long-term.

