#### **Clinical Effectiveness**

1. By the end of Phase 1, experimental study participants (Arm 1 & Arm 2) who adhered to their group exercise schedule should have greater improvements in primary outcomes compared to non-experimental study participants (Arm 3).
  - a. Improvements in primary outcomes include reduction in HbA1c levels, increase in VO2 max levels, and increase in self-reported physical activity levels.
2. By the end of Phase 1, experimental study participants who attended thrice-weekly group exercise sessions (Arm 2) should have greater improvements in primary outcomes compared to experimental study participants who attended once-weekly group exercise sessions (Arm 1).
3. By the end of Phase 2, experimental study participants (Arm 1 & Arm 2) who maintained their exercise schedule should have improved primary outcomes compared to non-experimental study participants (Arm 3).
4. By the end of Phase 2, experimental study participants who maintained thrice-weekly exercise sessions (Arm 2) should have greater improvements in primary outcomes compared to experimental study participants who maintained once-weekly exercise sessions (Arm 1).

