#### **Patient-Centered Outcomes**

1. By the end of Phase 1, study participants who attended thrice-weekly group exercise sessions (Arm 2) should report greater level of satisfaction with the IMPACT exercise program compared to study participants who attended once-weekly group exercise sessions (Arm 1).
2. By the end of Phase 1, study participants who attended thrice-weekly group exercise sessions (Arm 2) should report greater improvement in quality of life compared to study participants who attended once-weekly group exercise sessions (Arm 1).

3. By the end of Phase 2, study participants who maintained thrice-weekly exercise sessions (Arm 2) should report greater improvement in quality of life compared to study participants who maintained once-weekly exercise sessions (Arm 1).

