#### 4.1.c EXERCISE INTERVENTION MEASUREMENTS

Additional measurements will be collected from study participants specifically in the exercise intervention groups (Arm 1 and Arm 2). The following is a list of essential measurements to be collected over the course of the six-month exercise intervention period.

- Blood glucose control
  - Daily blood glucose levels
- Physical fitness
  - Strength
  - Exercise intensity
- Physical activity level
  - Activity type
  - Activity duration
  - Activity intensity
  - Activity location
- Resource utilization
  - Participant attendance
  - Staff presence

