## 4.2 STUDY INTERVENTION

### 4.2.a THE IMPACT EXERCISE PROGRAM

The study intervention is an exercise program developed by the IMPACT Study and reviewed by [name], PhD, [name], PhD, and [name], DPT, ACT, OCS. [name] is an expert in exercise physiology and exercise psychology and an Assistant Professor at Brown University. [name] is an expert in physiological science and an Associate Research Professor at UCLA School of Nursing. [name] has extensive expertise in physical therapy and is currently the Manager at the PAMF Physical Therapy Center.

The IMPACT Exercise Program is designed for study participants in Arm 1 and Arm 2 to engage in structured exercise activities in a clinical setting. The structured exercise sessions are led by instructors and conducted in groups. The entire exercise program is 26 weeks or approximately six months in length and will take place during Phase 1 of the study.

Once study participants are assigned to a study arm, they have entered Study Phase 1. Study participants in both Arm 1 and Arm 2 must schedule and undergo an initial exercise evaluation before beginning the exercise program.

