## **6.2 DATA ANALYTICAL METHODS**

### **6.2.a DATA ANALYSIS PLAN**

Statistical analyses will investigate clinical effectiveness of structured physical activity regimens across varying frequencies. The main statistical approach will be to date-match outcomes to concomitant exercise regimens, then to examine univariate and multivariate associations with changes in clinical outcomes, patient-centered outcomes, and cost. Statistical significance will be determined at  $P < 0.01$ , a stricter value due to the expected number of models used, or with other adjustments for multiple comparisons when applicable. Statistical analyses will be performed using SAS® (Cary, NC), and supplemented with STATA or Splus for methods not available in SAS®.

Study participants who are not able or willing to continue with the randomized frequency of intervention will be treated as loss to follow-up and only data obtained while in the assigned protocol will be used in the primary analysis (intention-to-treat). Since participants and non-participants continue to receive care within the healthcare system contemporaneously during the research study, IMPACT will obtain interstitial outcome data and complete clinical narrative through observational data available in the EHR. The statistical analysis will be conducted by Senior Statistician/s with the guidance of Biostatistical Consultant [name].

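### Three Phase 2 hypotheses compare undefined, self-selected participants who maintained their exercise; they should compare the arms as randomised

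*Protocol*

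**What the plan says.** **Hypotheses (protocol 2.3.b).** Three of the hypotheses for the end of Phase 2 are conditional on continued exercise.
- Clinical Effectiveness item 3: "experimental study participants (Arm 1 & Arm 2) who maintained their exercise schedule should have improved primary outcomes" compared with Arm 3.
- Clinical Effectiveness item 4: "By the end of Phase 2, experimental study participants who maintained thrice-weekly exercise sessions (Arm 2", compared with once-weekly maintainers in Arm 1.
- Patient-Centered Outcomes item 3: "study participants who maintained thrice-weekly exercise sessions (Arm 2) should report greater improvement in quality of life" than once-weekly maintainers in Arm 1.

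**Intervention and its records.** Section 4.2.a says: "The entire exercise program is 26 weeks or approximately six months in length and will take place during Phase 1 of the study". Section 4.1.c lists attendance and activity type, duration, intensity and location among the "essential measurements to be collected over the course of the six-month exercise intervention period".

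**Analysis (6.2.a).** The opening paragraph says: "The main statistical approach will be to date-match outcomes to concomitant exercise regimens". Under Study Aim 1, adherence means attending more than 80% of assigned structured sessions. The Statistical Analysis text there studies participants by randomised assignment and places re-analysis by actual attendance among the sensitivity analyses.

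**Phase 2 data.** Section 2.2.b says Arms 1 and 2 will be monitored in Phase 2 for whether activity continues. The schedule in 4.1.b marks the MAQ at months 12, 18 and 30. Section 3.2.b describes the MAQ as a three-month recall of types, frequency and duration of exercise.

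**The concern.** The condition in these hypotheses refers to a schedule that the study stops providing at month 6, and nothing replaces it. The groups to be compared at month 30 therefore have no stated membership rule.

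Any rule added later would select on behaviour after randomisation. People who keep exercising for two years without a programme are likely to differ in motivation and health from those who stop. Item 3 would set such a subset against the whole of Arm 3. Item 4 and the quality-of-life hypothesis would compare two subsets selected by conditions of different difficulty. In neither case does randomisation protect the comparison. A difference in HbA1c or quality of life could reflect who persisted rather than which contact frequency was assigned. The choice of contact frequency is what the trial is meant to inform.

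**Working it through.** No sample-size or alpha figure is involved. The check sets the sections side by side and counts.

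1. **Sessions that could be maintained.** Section 4.2.a gives 26 weeks, all in Phase 1. Assigned sessions are 26 × 1 = 26 in Arm 1 and 26 × 3 = 78 in Arm 2. The design diagram in 2.2.b shows no intervention in Phase 2, so none are assigned over the 24 months from month 6 to month 30. Nor does a home schedule take over: under Personal Exercise Regimen in 4.2.a the study neither encourages nor discourages independent exercise.

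2. **Whether the adherence rule carries over.** The threshold is more than 0.80 × 26 = 20.8 sessions in Arm 1 and more than 0.80 × 78 = 62.4 in Arm 2. With no assigned sessions after month 6, a percentage of assigned sessions does not exist in Phase 2. No other section defines *maintained*.

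3. **How many hypotheses are affected.** Section 2.3.b lists 4 clinical, 3 patient-centered and 3 cost-effectiveness hypotheses, 4 + 3 + 3 = 10. Clinical items 3 and 4 and patient-centered item 3 carry the condition: 3 of 10. The primary hypothesis in 2.3.a does not.

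4. **Date-matching.** Post-baseline visits fall at months 3, 6, 12, 18 and 30. At the last three (3 of 5) there is no assigned session regimen, so the only regimen to match is the one the participant chose and reported. Used as the main approach, this compares participants by self-chosen exercise. The Study Aim 1 text compares them by randomised arm. Both cannot be the main analysis.

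5. **What Phase 2 does observe.** The MAQ is scheduled at three Phase 2 visits with a three-month recall: 3 × 3 = 9 of 24 months. Change in self-reported activity is already a named process measure compared across the three arms. Exercise behaviour at month 30 is therefore recorded, in every arm.

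**The case against.** The strongest reply has four parts.

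- **The wording may mean self-directed exercise.** The Phase 1 hypotheses speak of group sessions; the Phase 2 ones drop the word *group*. Continued exercise at the earlier frequency is a plausible reading, and the MAQ can capture frequency. This stands. It removes any claim that the condition is impossible, but it makes the subset more plainly self-selected.
- **Defining *maintained* can be left to the statistical analysis plan.** As far as a cut-off goes, this also stands. It does not reach the comparison itself: the protocol states hypotheses about a post-randomisation subset, and a derived variable would leave them so.
- **Analysis by randomised assignment is already planned.** True for Study Aim 1. That is why the conditional hypotheses and the regimen-matching sentence need to be brought into line with it.
- **Exercise logs have no stated end date.** Section 2.2.a asks Arms 1 and 2 to update a log, but 4.1.c ties activity records to the six-month period, and Arm 3 is not asked to keep one.

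A reader might go further and infer that maintenance cannot be scored for anyone at month 30, or that the stated purpose, "to initiate and maintain physical activity recommendations long-term", has no endpoint. The documents do not support either. The MAQ is collected at months 12, 18 and 30, self-reported activity is a named measure, repeated-measures and mixed-effects models are planned, and HbA1c is measured at month 30.

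**Conclusion.** The point holds as a fault in how the Phase 2 comparisons are framed. Three of the ten secondary hypotheses rest on groups that are undefined and, however defined, self-selected after randomisation. The regimen-matching described as the main approach has the same weakness at three of the five post-baseline visits and conflicts with the randomised-assignment analysis in the same section. The primary hypothesis is not affected by the condition, and the two years of follow-up are not wasted, because the data needed for a randomised comparison are already scheduled.

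The size of the bias cannot be computed: the protocol gives no expected proportion of maintainers and no figure for how they differ from others. The conclusion assumes that the six-month limit in 4.1.c covers attendance and activity records, as it reads, and that continuing to exercise is related to the outcomes.

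**What to change.** 1. **2.3.b.** Restate clinical items 3 and 4 and patient-centered item 3 as comparisons of the arms as randomised at month 30, using all participants.
2. **6.2.a, opening paragraph.** Make randomised arm the main exposure at every visit, and keep date-matching to concomitant regimens as a sensitivity analysis, next to the attendance-based re-analysis already listed there. The following paragraph, which limits the primary analysis to data obtained under the assigned protocol, needs to be reconciled with this; otherwise not all participants would be used.
3. **Secondary descriptive measure.** Report, by randomised arm, the proportion whose MAQ at months 12, 18 and 30 meets the recommendation cited in 1.1.b and 1.2.a: at least 150 minutes per week of moderate aerobic activity and resistance exercise at least twice a week. The exact derivation can sit in the statistical analysis plan.

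The cost is protocol wording and one derived variable, with no new visit or instrument. State the limits of the measure: the MAQ is self-reported and covers about 9 of the 24 Phase 2 months. The description in 3.2.b also does not list intensity, so moderate activity may have to be inferred from activity type.

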#### **Patient-Centered Outcomes**

1. By the end of Phase 1, study participants who attended thrice-weekly group exercise sessions (Arm 2) should report greater level of satisfaction with the IMPACT exercise program compared to study participants who attended once-weekly group exercise sessions (Arm 1).
2. By the end of Phase 1, study participants who attended thrice-weekly group exercise sessions (Arm 2) should report greater improvement in quality of life compared to study participants who attended once-weekly group exercise sessions (Arm 1).

3. By the end of Phase 2, study participants who maintained thrice-weekly exercise sessions (Arm 2) should report greater improvement in quality of life compared to study participants who maintained once-weekly exercise sessions (Arm 1).

### **Cost-Effectiveness**

1. Based on the percentage of reduced HbA1c levels, the experimental interventions (Arm 1 & Arm 2) should be more cost-effective compared to the non-experimental intervention (Arm 3).
2. Based on the percentage of reduced HbA1c levels, the once-weekly group exercise intervention (Arm 1) should be more cost-effective compared to the thrice-weekly group exercise intervention (Arm 2).
3. Based on quality of life, the once-weekly group exercise intervention (Arm 1) should be more cost-effective compared to the thrice-weekly group exercise intervention (Arm 2).

## **2.4 STUDY POPULATION**

### **2.4.a STUDY POPULATION**

The population for the IMPACT study consists of individuals who seek care at Stanford Hospitals and Clinics (SHC) and are diagnosed with T2DM.

## 2.4.b POTENTIAL PARTICIPANTS

Potential study participants for the IMPACT study are patients within the SHC healthcare system. IMPACT will work with the Stanford Center for Clinical Informatics (SCCI) to generate a list of potential participants. Using the EpicCare EHR, the SCCI will query for SHC patients according to the initial screening criteria:

- Alive as of 2016
- Between 30 to 65 years of age
- At least one visit to the SHC in the past two years
- Type 2 diabetic as defined by one or more of the following:
  - Diagnosis of Type 2 Diabetes mellitus (ICD-9 code: 250.X0, 250.X2)
  - Type 2 Diabetes mellitus defined as any two abnormal laboratory values:
    - Hemoglobin A1c results  $\geq 6.5\%$
    - Fasting blood glucose results  $\geq 126$  mg/dL
    - Random blood glucose  $\geq 200$  mg/dL
    - Oral glucose tolerance test  $\geq 200$  mg/dL
  - Current continuous use of any oral anti-diabetic medication
- Recent Hemoglobin A1c (HbA1c) results between 6.6-9.9%

The SCCI will exclude SHC patients with:

- Long-term current use of insulin (ICD-9 code: V58.67)
- BMI  $> 70$  kg/m^2
- Clinical diagnosis of atrial fibrillation (ICD-9 code: 427.3)
- Current pregnancy (ICD-9 code: V22.X)
- Serious concurrent illnesses likely to cause death within the next 5 years (ie. Terminal cancer or obstructive airway disease)

The resulting potential participant list will include the following SHC patient information:

- First Name
- Last Name
- Date of Birth
- Mailing Address
- Contact Telephone Number
- Email address
- Name of Primary Care Provider
- Health Insurance Status
- Preferred Language
- Date of Last HbA1c Value

## 2.4.c INCLUSION AND EXCLUSION CRITERIA

The purpose of establishing inclusion and exclusion criteria is to define the participant population to be used for the research study. In order for a potential participant to become an eligible participant in the IMPACT study, he or she must meet all of the final eligibility criteria:

- Has primary care physician at SHC
- Diagnosed with Type 2 diabetes
- HbA1c between 6.6 and 9.9%
- Between 30 to 65 years of age
- Has ability to communicate with study staff, sign informed consent, and accept randomization
- Free of intervening events (ie. a sick spouse)
- Willing to exercise at Cardiac Therapy Foundation (CTF) up to three times a week for six months
- Willing to attend all study visits

The IMPACT study has also defined criteria that would exclude an individual from becoming eligible for the study. The criteria for study exclusion are:

- Insulin-dependent
- Resting heart rate  $\geq 120$  beats per minute (bpm)
- Blood pressure  $\geq 180/100$  mm Hg
- History of or present heart or cardiovascular problems
- History of or present respiratory disease
- History of or present spinal cord injury
- History of stroke or Transient Ischemic Attack (TIA)
- History of cancer diagnosis in the past 5 years or present cancer diagnosis
- Medical, psychiatric, behavioral limitations that may interfere with study participation
- Participating in other clinical trials that may interfere with study procedures and outcomes
- Currently pregnant or plans to become pregnant within three years
- Plans to be away more than four weeks in the next nine months
- Plans to leave the community within five years

## 2.4.d PARTICIPANT SPECIFICATION

The individuals within the study population have a different designation as they move along the initial processes of recruitment. These designations include: (1) SHC Patients, (2) Potential Participants, and (3) Study Participants.

### **SHC Patients**

SHC Patients are individuals who are a part of the Stanford Healthcare system.

### **Potential Participants**

Potential Participants are SHC Patients who meet the initial screening criteria. These individuals remain as “Potential Participants” throughout the recruitment and baseline visit processes.

### **Study Participants**

Study Participants are Potential Participants who meet the final eligibility criteria. These individuals become “Study Participants” after completing and meeting all criteria during the baseline visit.

[figure not shown]

## **Chapter 3: Participant Recruitment and Enrollment**

## **3.1 PARTICIPANT RECRUITMENT**

### **3.1.a PRIMARY RECRUITMENT METHODS**

Primary recruitment methods for the IMPACT study are designed specifically for potential participants. Postal mail will be used for this method. The aim is to provide study information and generate interest from individuals who are likely eligible for the IMPACT study.

#### **POSTAL MAIL RECRUITMENT LETTERS**

SCCI will query patient population data and generate a list of study-eligible patients, based on inclusion/exclusion criteria. Once a patient has been identified as a prospective study participant, the PI / study team will obtain approval from the primary care provider (PCP) for contacting his or her patient.

Upon PCP approval, a letter will be sent to potential participant's mailing address. This letter of invitation will explain the purpose of the study and will invite interested participants to contact the PI / study team. In addition to the letter of invitation, potential participants will also receive a return-addressed postcard, allowing potential participants to indicate their interest or disinterest in the research study. Study staff will not contact participants who reply to the postcard and indicate their disinterest in the study and in being contacted.

### **3.1.b SECONDARY RECRUITMENT METHODS**

Secondary recruitment methods for the IMPACT study are designed for the general population. The aim is to raise awareness and identify potential participants through alternate avenues. Depending on the response rate from the primary targeted recruitment methods, secondary recruitment methods may be implemented. Secondary methods to be used for the study include a study webpage, social media, primary care provider, and flyers and brochures.

#### **STANFORD WEBPAGE**

IMPACT staff will create a website based on Stanford domain ([www.stanford.edu](http://www.stanford.edu)) providing information, methods, objectives of the IMPACT study. This webpage will be updated periodically to provide information on the developments of the IMPACT study.

#### **SOCIAL MEDIA**

Facebook and Twitter are the social media recruitment components for the study. The study may utilize social media outlets to announce the commencement and developments of the study. Each social media outlet will include the IMPACT web link to direct readers to information about the study.

#### **PRIMARY CARE PROVIDERS**

IMPACT study staff may hold informational meetings with primary care providers and medical assistants to enlist their assistance in referring appropriate patients for the study.

## FLYERS AND BROCHURES

Flyers and brochures containing IMPACT study information may be posted and placed in the clinics and labs waiting areas likely to capture the attention of type 2 diabetes mellitus (T2DM) patients (e.g., internal medicine, family medicine, endocrinology). In order to post flyers and place brochures at specific departments, IMPACT staff members will meet with and gain the approval of the relevant department directors.

### 3.1.c TELEPHONE SCREENINGS

The main purpose of the telephone screening is to inform potential participants of the IMPACT study and determine whether they meet inclusion and exclusion criteria and are study-eligible participants. The telephone screen consists of:

- Greetings and introduction
- Purpose of telephone call
- Brief overview of IMPACT study
- Study description (*when patient is interested in learning more about IMPACT*)
- Screening questions (*when patient is interested in participating in IMPACT*)
- In-person baseline visit scheduling (*when patient is deemed eligible for the baseline visit*)

Telephone screenings are conducted with potential participants who:

- Indicated their interest through direct contact by responding via postal mail and/or telephoning the IMPACT study

If the individual meets the preliminary eligibility criteria based on the screening questions, he or she may continue the study eligibility process. The potential participant will be invited to schedule and attend a study baseline visit to continue the eligibility assessment process. The potential participant is then asked to attend the study baseline visit to begin the assessment process to determine eligibility in study participation.

If the individual does not meet the preliminary criteria based on the screening questions, he or she will not be eligible to participate in the study. If a potential study participant completed an online eligibility questionnaire and did not meet the preliminary criteria, IMPACT study staff will contact that individual to inform them of their ineligibility. The recruitment list will be updated so that participants in the “Do Not Call” list will not be further contacted by IMPACT.

